### Statistical analysis

The aim of this pilot trial is to achieve data on the efficacy of both therapies. The effect of treatment on primary and secondary outcomes will be described by mean, standard deviations and confidence intervals per treatment group. These parameters and a definition of a clinically non-relevant difference will be used for sample size calculation of a randomized phase III trial to show non-inferiority of moderate aerobic endurance training versus relaxation training in patients with migraine [24].

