## Abstract

**Background:**

Migraine is one of the most frequent headache diseases and impairs patients’ quality of life. Up to now, many randomized studies reported efficacy of prophylactic therapy with medications such as beta-blockers or anti-epileptic drugs. Non-medical treatment, like aerobic endurance training, is considered to be an encouraging alternative in migraine prophylaxis. However, there is still a lack of prospective, high-quality randomized trials. We therefore designed a randomized controlled trial to evaluate the efficacy of aerobic endurance training versus relaxation training in patients with migraine (ARMIG).

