## Design

This is a single-center, open-label, prospective, randomized study on the prophylactic effect of moderate aerobic endurance training versus relaxation training in patients with migraine.

The procedures and design of the study were approved by the Medical Ethics Committee of the University of Duisburg-Essen in Essen, Germany (Approval number 11–4677) and the study is internationally registered (ClinicalTrials.gov, Registration number NCT01407861).

The study started in July 2011, and participants are recruited via local newspapers, study brochures or local television. Interested participants are informed about the study protocol. After written informed consent, a sport therapist will make an appointment to conduct an endurance test to determine the optimal training heart rate. Participants will be examined by a neurologist to confirm the diagnosis of migraine and to check inclusion and exclusion criteria (see below). Diagnosis of migraine is based on the International Classification of Headache Disorders criteria (ICHD-II) [14].

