### Exclusion criteria

Exclusion criteria are as follows:

1. Diseases or disabilities that disqualify for performing either aerobic endurance training or relaxation training (that is, severe asthma, pacemaker, major depression, specific physical handicap)

2. Language disabilities that disenable filling out questionnaires

3. Fewer than three migraine days per month

4. Pregnancy

5. Additional diagnosis of secondary headache according to the ICHD-II (that is, medication overuse headache)

6. Prophylactic headache medication started within the last 12 weeks

7. Regular performance of endurance training and/or relaxation training at least twice a week

Migraine patients who are stable on prophylactic medication and meet the inclusion and exclusion criteria may be enrolled. Participants will be asked to keep a headache diary during the whole study period. Randomization will be performed at the end of the 4-week baseline period. Each participant will receive a sealed envelope. Randomization sequence is composed by an independent statistician using computer-generated random numbers. Participants are randomized to either the endurance training or the relaxation training group (1:1). Overall, 60 participants are planned to be enrolled in the trial. This is considered as a pilot trial to prove the feasibility of such a trial design and to achieve data on efficacy of both therapies.

The treatment (training) period will begin after baseline headache diary documentation for at least 4 weeks to obtain baseline number of headache days. Training will be in groups of up to 10 participants (Figure 1).

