### Primary outcome measure

The primary outcome measure is a reduction of headache days in the last 4 weeks of the 12-week training compared to baseline (4 weeks before the start of training).

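### Per-arm summaries are labelled the treatment effect, and the article states no between-arm difference in headache days, the quantity that randomisation protects

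*Protocol article*

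**What the plan says.** The aim is comparative. The abstract says the trial was designed to "evaluate the efficacy of aerobic endurance training versus relaxation training in patients with migraine", and the Design section describes a "randomized study on the prophylactic effect of moderate aerobic endurance training versus relaxation training in patients with migraine". Allocation is 1:1 to two active arms, and the Discussion explains why no waiting-list arm was used.

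The section on the primary outcome defines it as "a reduction of headache days in the last 4 weeks of the 12-week training compared to baseline (4 weeks before the start of training" (the bracket closes there), so each participant contributes a change from baseline.

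The Statistical analysis section then fixes how the effect will be expressed: "The effect of treatment on primary and secondary outcomes will be described by mean, standard deviations and confidence intervals per treatment group". It continues: "These parameters and a definition of a clinically non-relevant difference will be used for sample size calculation of a randomized phase III trial", and says that trial is to show non-inferiority of endurance to relaxation training. No between-arm difference is named.

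The text after the exclusion criteria gives the trial's status: "This is considered as a pilot trial to prove the feasibility of such a trial design and to achieve data on efficacy of both therapies".

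**The concern.** The sentence on the effect of treatment names a quantity and a way of estimating it, and the two do not match. In a trial with two active arms and no untreated arm, the average change in one arm is not the effect of that arm's training. It also contains whatever would have happened over the same months without it. This matters here because entry requires at least three migraine days per month, so participants may tend to enter in a worse-than-usual period, and because daily diary keeping can itself change what is recorded.

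Two things are at stake. First, an improvement in each arm could be reported as efficacy of each therapy, which the design cannot show. Second, the comparison that the trial was randomised to make, and that the later non-inferiority trial rests on, would have no stated estimate and no stated measure of uncertainty.

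**Working it through.** **Figure to reproduce.** None. The total of 60 is given without significance level, power, effect size or SD. The Discussion supports it only by the equal number used in the cited Swedish trial.

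**What a per-arm change contains.** Write the expected change in the endurance arm as E + c and in the relaxation arm as R + c. E and R are the training effects, and c is the change that would occur anyway (natural course, diary effects, regression to the mean).

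- A per-arm summary estimates E + c or R + c. Without an inactive arm, c cannot be separated out.
- The difference is (E + c) − (R + c) = E − R. Randomisation makes c equal in expectation in the two arms, so it cancels.

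**Precision inputs.** From the document: n = 30 per arm, 1:1. Assumed: two-sided 95% intervals, an equal SD of the 4-week headache-day count in both arms and both periods, and a baseline-outcome correlation r of 0.3 to 0.7. The document gives no SD, so results are in SD units.

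**Per-arm and between-arm half-widths.**

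- One arm: t(0.975; 29)/√30 = 2.045/5.477 = 0.373 SD.
- Difference: t(0.975; 58) × √(2/30) = 2.002 × 0.258 = 0.517 SD.
- Ratio: 0.517/0.373 = 1.38. It is the same if change scores are summarised, because both half-widths scale by the same factor.

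For scale only: at an assumed SD of 3, 4 or 5 days, the difference half-width is 1.55, 2.07 or 2.58 days, and the per-arm half-width is 1.12, 1.49 or 1.87 days.

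**Gain from baseline adjustment.** The variance of a change score is 2(1 − r) times that of the final count. The residual variance in analysis of covariance is (1 − r²) times it. The ratio is (1 − r²)/[2(1 − r)] = (1 + r)/2. Half-widths below are for the between-arm difference with 30 per arm.

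| r (assumed) | Change score, SD units | ANCOVA, SD units | Variance ratio | Variance saved |
|---|---|---|---|---|
| 0.3 | 0.517 × √1.4 = 0.61 | 0.49 | 0.65 | 35% |
| 0.5 | 0.517 × √1.0 = 0.52 | 0.45 | 0.75 | 25% |
| 0.7 | 0.517 × √0.6 = 0.40 | 0.37 | 0.85 | 15% |

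The ANCOVA column is 0.517 × √(1 − r²), with one fewer degree of freedom.

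**Loss to follow-up.** The article states no rate of its own. It quotes 85% completing training and about 70% with 3-month data in the Swedish trial. Applied here, 30 × 0.85 = 25.5 per arm gives an unadjusted difference half-width of 0.56 SD, and 30 × 0.70 = 21 per arm gives 0.62 SD.

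**The case against.** The strongest reply is that this is a declared pilot. Confirmatory comparison is deferred to a later trial, and the main data input to that trial's sample size is the outcome SD, which per-arm description supplies. The article is also condensed: the choice of model, the analysis set and further covariates normally belong to a fuller plan that is not shown. A difference in change scores is itself unbiased under randomisation, so covariate adjustment is a gain in precision and not the repair of a bias.

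Most of this stands. No formal test is needed, its absence is no fault, and the missing modelling detail is not held against the article. What does not fall to it is the sentence itself. It states what the effect of treatment is and places it within each arm. A fuller plan could add a model, but the sentence would still attach the wrong label.

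A reader might go further in four ways that the document does not support.

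- *The baseline is ignored.* It is not: the primary outcome is a change from it. Only its use as a covariate is not stated.
- *The trial can never estimate its own contrast.* The article states no contrast but excludes none. An unadjusted difference and its interval follow from the arm means, SDs and numbers.
- *The arms will be called equally effective because their intervals overlap.* No section plans to judge overlap, and the Statistical analysis section says that a clinically non-relevant difference has to be defined for the later trial.
- *A particular number of days of improvement will be regression to the mean.* The inclusion criterion says that patients report three migraine days. It does not say that the baseline diary month is the entry test, and the outcome counts headache days. The size of any such effect cannot be fixed from the document.

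**Conclusion.** The point holds in a limited form. The article labels within-arm summaries as the effect of treatment in a randomised comparison of two active therapies, and does not state the between-arm difference or its interval. The mismatch follows from the text and needs no assumed figures.

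The size given to it does rest on assumptions. The uncertainty about the contrast is about 1.38 times that of one arm (0.52 against 0.37 SD), given 30 analysed per arm and equal SDs. The saving of 15% to 35% from baseline adjustment depends on an assumed correlation of 0.3 to 0.7.

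This should be corrected before analysis. It does not undermine the design, and the pilot purpose keeps it from being more serious.

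**What to change.** Reword the Statistical analysis section along these lines: *The effect of treatment is the difference between the endurance and relaxation arms in mean headache days in the last 4 weeks of training, with its 95% confidence interval, estimated by analysis of covariance adjusted for baseline headache days. It is reported as a pilot estimate and not as a confirmatory test. Means and standard deviations in each arm are given for description and for planning the later trial; a change from baseline within an arm is not taken as evidence of efficacy.*

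Bring the stated aim, "to achieve data on efficacy of both therapies", into line, so that it speaks of the comparison and of planning data and not of the efficacy of each therapy separately.

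The cost is a change of wording and one additional model. The baseline diary is already collected, and no further participants or visits are needed. The model also gives the residual SD, which is the relevant planning input if the later trial is analysed in the same way.

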## Discussion

This is a German single-center trial to study the prophylactic effect of moderate aerobic endurance training versus relaxation training in patients with migraine. We chose two active arms for comparison instead of inactive ‘waiting lists’ as placebo because inactive control groups would bear a high risk of withdrawal from the trial. Furthermore, relaxation training has proven to be effective in migraine treatment [3,11-13] and facilitates comparability, in contrast to medical treatment or ‘just taking a pill’, especially when done in a similar setting to exercise training. The study outcome depends on regular participation in either the exercise or the relaxation training group over a period of 12 weeks. Considering that all of the participants have not performed sports or relaxation training on regular basis before, a relevant drop-out rate cannot be ruled out. In the Swedish trial by Varkey *et al.*, only 85% completed the training, data on about 70% of the participants were collected at follow-up after 3 months, and only 50% of the participants returned questionnaires after 6 months [9]. Compared to the Swedish trial where relaxation training was performed individually, in our trial both exercise and relaxation training will mainly take place in a supervised group to rule out bias due to group dynamics. The overall number of 60 participants (30 in each study arm) may influence the significance of the results. However, Varkey *et al.* used an equal number of participants in their migraine exercise trial. Depending on our results, a multicenter trial with the same protocol may be planned.

## Trial status

Recruitment of participants started in July 2011 and is expected to end in summer 2012.

## Abbreviations

AT: [name]; CG: [name]; CRF: Case report form; FFB-Mot: Fragebogen zum motorischen Funktionsstatus (motor fitness questionnaire); HADS: Hospital Anxiety and Depression Scale; HIT-6: Headache Impact Test 6; HSLC: Headache-Specific Locus of Control Scale; ICHD-II: International Classification of Headache Disorders (second edition); PDI: Pain Disability Index; PMR: Jacobson’s Progressive Muscle Relaxation; PWC: Physical Working Capacity; SF-12: Short form 12.
